### 8.3. PATIENT REPLACEMENT POLICY

All included patients who have been withdrawn prior to randomization or once randomized if you have not received any doses of the IEP. Therefore, no patient who withdraws, after receiving the assigned treatment, because of side effects or ineffectiveness of treatment. For patient replacement, a mirror list will be developed in the randomization system.

### 8.4. TRIAL INTERRUPTION

The study will be interrupted if any of the following circumstances are met:

1. Serious toxicity (grade 3-4 NCI CTC-AE) related to investigational drug in 3 patients.
2. Serious infections (grade 3-4 NCI CTC-AE) related to the administration procedure in 3 patients.
3. Investigational drug-related mortality in 1 patient

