## 12.2. DEFINITIONS

An adverse event (AE) is defined as any adverse medical episode or experience in a patient or clinical trial subject receiving the experimental treatment (including the comparator group), even if it does not necessarily have a causal relationship to that treatment. This may include any unfavorable or unintentional signs or symptoms, an abnormal laboratory finding (including blood tests, x-rays, or scans), a temporary illness associated with the use of study cell therapy, or a worsening of a pre-existing condition. A disorder

Persistent is a clinical condition (including a disorder being treated) that was diagnosed before the subject signed informed consent and is documented in the subject's medical history. In addition, any event associated with an overdose of the product will also be considered an adverse event.

Medical or surgical procedures (e.g., endoscopy or appendectomy) are not considered an adverse event; The adverse event is the medical condition that gives rise to the procedure.

A procedure-related adverse event is an AE that appears during a study

It is not related to the investigational product, but which, in the opinion of the investigator, is related to some procedure of the trial. For example, a harmful episode that

It is related to a medical procedure required by the protocol such as the surgical conditioning of the patient necessary to administer the investigational drug. The AEs considered as related to the procedure will be analyzed in isolation, although they will be considered a part of the total related AAs of the study.

Adverse Reaction (AR) An AR is any harmful, unintended reaction to an investigational drug, regardless of the dose administered. Unlike an AE, there is a causal relationship to the investigational drug (possible, probable, or certain relationship).

A Serious Adverse Event (SAE) is defined as any unwanted experience that affects a patient, whether or not it is considered related to the treatment of the protocol and that results in:

- Death.
- A life-threatening event (i.e., there was a risk of immediate death of the patient at the time the reaction was observed).
- Hospitalization or prolongation of a hospitalization.
- Persistent or significant disability/incapacity.

- A congenital anomaly or a birth defect in descendants.

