For causation assessments, events that meet the categories of safe, probable or possibly will be considered "related". Events that are improbably related or unrelated will be considered unrelated. If the investigator believes that a SAE is likely to be unrelated (unlikely related) or unrelated to the study drug, he or she must provide an alternative cause for the study.

The intensity or severity of AEs should be classified according to the common terminological criteria for Events Adverse (CTCAE) Version in effect (

[https://ctep.cancer.gov/protocolDevelopment/electronic\\_applications/ctc.htm](https://ctep.cancer.gov/protocolDevelopment/electronic_applications/ctc.htm) ). If they are not described, the following definitions may be used to qualify the severity of each AE:

|         |                                                                                                                                                                                                            |
|---------|------------------------------------------------------------------------------------------------------------------------------------------------------------------------------------------------------------|
| Grade 1 | Slight; asymptomatic or mild symptoms, only clinical or diagnostic observations, no intervention indicated.                                                                                                |
| Grade 2 | Moderate; minimal, local or non-invasive intervention; limitation of the instrumental activity of daily life.                                                                                              |
| Grade 3 | Severe; severe or of medical significance but not an immediate threat to the life; hospitalization or prolongation of hospitalization indicated; incapacitating; Limitation in self-care of daily activity |
| Grade 4 | Life-threatening; Urgent intervention required                                                                                                                                                             |
| Grade 5 | Death                                                                                                                                                                                                      |

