A distinction must be made between the severity and severity of AEs. An AE that is evaluated as Grade 4 (life-threatening) should not be confused with an SAE. Severity is a category used to rate the intensity of an event; and both an AE and an SAE can be assessed as Grade 4. An event is defined as "serious" when it meets one of the criteria described above in Section 16.2

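### Section 8.4 has no automatic interruption criterion for a fatal infection attributed solely to the administration procedure

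*Protocol*

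**What the plan says.** Protocol section 8.4 opens with "The study will be interrupted if any of the following circumstances are met" and lists three circumstances:

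- Item 1: "Serious toxicity (grade 3-4 NCI CTC-AE) related to investigational drug in 3 patients".
- Item 2: "Serious infections (grade 3-4 NCI CTC-AE) related to the administration procedure in 3 patients".
- Item 3: "Investigational drug-related mortality in 1 patient".

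Three definitions elsewhere decide which events these items reach.

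- Section 12.2 describes a procedure-related adverse event in these terms: "It is not related to the investigational product, but which, in the opinion of the investigator, is related to some procedure of the trial". The drug-related and procedure-related categories thus exclude each other.
- Section 12.3 gives a five-step severity table in which grade 5 is death.
- Section 12.3 also says what counts as related: "events that meet the categories of safe, probable or possibly will be considered" related. Improbable and unrelated events do not count.

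Two safeguards sit outside section 8.4. Section 1.16 sets up a DSMC that oversees periodic safety reviews and may recommend stopping. Section 12.5.2 requires serious adverse events to reach the sponsor within 24 hours, whatever their cause.

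**The concern.** An interruption rule should not become less sensitive as the event becomes worse. Item 2 recognises infection from the administration procedure as a harm worth counting, but its grade range ends one step below death. Item 3 recognises death, but only when the drug is held responsible. An infection caused by the procedure that ends in death falls between the two.

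Safety is a main objective (section 4.1), and section 5.3 says there are no previous studies. Section 8.4 holds the only numerical trial-level safety limits in the protocol. The administration procedure in section 9.5 and Annex 2 includes washing, possible debridement, and trimming and placing the sheet. When a wound under the sheet becomes infected, telling the product from its handling may be hard. For a fatal case, that attribution decides whether the mandatory rule applies.

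**Working it through.** The protocol derives no figure for these limits, so there is none to reproduce. The check is to read each item literally against the definitions.

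Inputs:

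- Item 1 needs drug-related attribution, grade 3 or 4, and a count of 3 patients (8.4).
- Item 2 needs an infection, procedure-related attribution, grade 3 or 4, and a count of 3 patients (8.4).
- Item 3 needs death, drug-related attribution, and a count of 1 patient (8.4).
- Death is grade 5 (12.3).
- Procedure-related means not product-related (12.2).
- Related means possible, probable or certain (12.3).

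One patient with each kind of event then contributes as follows:

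| Event in one patient | Item 1 (limit 3) | Item 2 (limit 3) | Item 3 (limit 1) | Interruption? |
|---|---|---|---|---|
| Grade 3-4 toxicity, drug-related | 1 | 0 | 0 | No, but 1 of 3 counted |
| Grade 3-4 infection, procedure-related | 0 | 1 | 0 | No, but 1 of 3 counted |
| Fatal infection, product at least possibly related | 0 | 0 | 1 | Yes |
| Fatal infection, procedure only | 0 | 0 | 0 | No, and nothing counted |

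The last row in steps:

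1. Item 1 fails twice. The event is not drug-related (12.2), and grade 5 is not in the range 3-4.
2. Item 2 fails on grade. The event is an infection and is procedure-related, but 5 is outside 3-4.
3. Item 3 fails on attribution. There is a death, but not one related to the investigational drug.

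With k such deaths and no other events, the three counts stay at 0, 0 and 0 for every k. Read literally, no number of them triggers interruption.

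A generous reading does not close the gap. If grade 5 is read into item 2, or if the infection was recorded at grade 4 before the patient died, each death adds 1 to that count. One death gives 1 < 3 and two give 2 < 3, so neither interrupts the trial. A single drug-related death gives 1 ≥ 1 under item 3 and does.

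**The case against.** The strongest reply is that the gap is narrow and lies within a wider safety system. Much of this stands.

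- Because possible counts as related (12.3), a fatal infection with any reasonable suspicion of the product triggers item 3 with one patient. The gap needs an investigator who judges the product improbable or unrelated.
- Section 8.4 lists sufficient conditions and does not say the trial can be interrupted only then. The DSMC can recommend stopping, and its work plan is not available here. A death is a serious adverse event and reaches the sponsor within 24 hours.

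These points limit the consequence to the automatic rule. They do not repair it: the committee's recommendation is discretionary and the 24-hour duty concerns reporting, whereas section 8.4 is written as mandatory. Nor can it be said that death is obviously implied in item 2, because item 3 deals with death separately and restricts it to the drug.

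A reader might infer more than this. Three stronger readings are not supported.

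- *That separate counts for drug and procedure contradict section 12.2.* That section does place procedure-related events within the related total ("although they will be considered a part of the total related AAs of the study"), but the same sentence says they are analysed in isolation. Separate counts agree with that.
- *That the limits are too loose because 2 patients with drug toxicity and 2 others with procedure infection, 4 in all, would not interrupt the trial.* The sum is right, but calling it an error presupposes a pooled limit that the protocol does not set. Any probability attached to it would rest on event rates the protocol does not give. The denominator is also unclear, since cleaning, debridement and compression are given in both arms (section 9.6 and Annex 4).
- *That items 1 and 2 confuse seriousness with grade.* Section 12.3 does separate the two, but its English text reads "A distinction must be made between the severity and severity of AEs", which suggests that translation merged two terms. The bracketed grades in section 8.4 show the intended criterion well enough.

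**Conclusion.** The point holds in a limited form. A fatal infection attributed solely to the administration procedure meets 0 of the 3 mandatory criteria in section 8.4, although grade 3-4 infections of the same cause count towards item 2 and one drug-related death is enough under item 3. This follows from the wording of sections 8.4, 12.2 and 12.3 and needs no assumed event rate. It rests on two conditions: the items are applied as written, and the product is judged improbable or unrelated.

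It would be too strong to infer that the trial would in practice carry on unexamined after such a death. DSMC review and rapid reporting stand, and the documents do not show how the sponsor would act. The fault is an inconsistency in a stated safety rule. It should be fixed, but it does not show that safety oversight is absent.

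**What to change.** Reconcile section 8.4 with sections 12.2 and 12.3. The grade range and attribution terms of items 2 and 3 should use the categories defined there and state explicitly how a grade 5 procedure-related event is handled. The DSMC work plan should carry the same wording. What the limit should be is for the sponsor and the DSMC to decide; none is proposed here.

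The cost is protocol wording and alignment of the work plan, with no new data and no additional patients. The one downside is that an interruption for review may be triggered slightly more often.

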## 9. DESCRIPTION OF THE TREATMENT

### 9.1. INVESTIGATIONAL THERAPY

- Investigational product: Adult mesenchymal stem cells of adipose tissue expanded in a biological matrix of fibrin-hyaluronic acid.
  - Fantasy name: BAMS, *Bioengineered Artificial Mesenchimal Sheet*.

- Active substance: Expanded adult trunk mesenchymal cells of adipose tissue.
- Pharmaceutical form: Equivalent of living tissue.
- Administration: Topic.
- Schedule: 4 administrations: one sheet will be administered weekly. Each patient assigned to the experimental treatment group will receive 4 slides at a concentration of about 360,000 cells/cm^2. The BAMS has a surface area of 21cm^2 and contains a total of 7.5 x 10^6 ADSCs.
- Manufacturer of the product under investigation: UPCIT of the Virgen de las Nieves University Hospital.

## 9.2. COMPARATOR

Conventional treatment (Annex 4).

## 9.3. PERMITTED AND PROHIBITED CONCOMITANT TREATMENTS

### 9.3.1. PERMITTED CONCOMITANT TREATMENTS

Jobst Compri2® compression therapy as standard, at 40 mmHg in all cases. Multi-layer compression therapy that provides effective compression for up to 7 days, with the first layer being a padded bandage and the second a cohesive compression bandage.

In case of infection of the ulcer, the administration of oral antibiotics should be allowed to avoid excessive manipulation of the site and the wound.

Protocol code: UV/AP/21

EudraCT: 2021-001341-12

Version of July 15, 2024.

### 9.3.2. PROHIBITED CONCOMITANT TREATMENTS

The administration of cytostatic and/or cytotoxic drugs and the typical use of corticosteroids at the site of injury are not permitted.

### 9.4. INVESTIGATIONAL PRODUCT IDENTIFICATION

The identification and labelling of the investigational product is detailed in Annex IV.

### 9.5. PROCEDURE FOR ADMINISTERING the IEP

Firstly, exudate will be collected from the wound, to be subsequently studied. After that, the following steps will be carried out:

Cleaning and washing of the wound with normal saline solution, NaCl 0.9% (NaCl 0.9%; BraumTM, 346056); exerting sufficient pressure so that waste or debris is dragged without damaging the wound tissue.

If necessary, mechanical debridement of the devitalized or unrevitalized areas shall be carried out.

Healing viability to create an ideal environment for the promotion of the healing process.

Determination of the wound area by means of a graduated ruler, measuring the greatest vertical length (length) and the longest perpendicular length (width), multiplying both lengths.

Application of the sheet of expanded ADSCs in the biological matrix of fibrin on the basis of the wound.

Hyaluronic acid. The placement will be carried out in such a way that it covers the entire bed of the ulcer and the periphery. The matrix prepared will be provided by the UPCIT in a simple packaging. The professional in charge of placing the wound will only have to adapt it to the area of the injury.

Wound coverage with a non-adhesive secondary polyurethane foam appliance (New Cutimed® Siltec Plus 73288/001) and Jobst® Compri2® 40mmHg compression therapy.

The day of the first application of treatment will be 0; from that moment on, the same procedure every 7 days until 4 weeks of treatment is completed. The weekly dose to be received will be a 21cm^2 sheet with 7.5x10^6 ADSCs.

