## ANNEX 2: STANDARD PROCEDURE FOR ADMINISTRATION OF THE INVESTIGATIONAL MEDICINAL PRODUCT.

1. Remove the compression therapy and then the apôsite that covers the injury. Perform the technique carefully, taking care not to damage the wound bed or the perilesional skin.
2. Sample collection of exudate: with filter paper (Fisherbrand™, Fisher Scientific S.L., Madrid, Spain):
  - Exudate samples should be taken from the ulcer bed by absorption with filter paper (500-1000 ul).
  - Place the filter paper over the injury. It is only necessary to place it, it is not necessary to rub.
  - One minute after the application of the absorbent paper, it shall be placed in 0.5 mL of cold phosphate-buffered saline solution.
  - The samples will be stored at a minimum temperature of -20°C until analysis.
3. Cleaning and washing of the wound with normal saline solution (NaCl 0.9%), exerting sufficient pressure to allow the dragging of debris or debris without damaging the wound tissue.
4. Mechanical debridement of devitalised or non-viable areas of scarring:
  - Gently rub the area of the injury on which you want to perform the technique
  - Wash away non-viable tissue debris
  - Perform a second cleaning of the injury with normal saline solution (NaCl 0.9%), exerting enough pressure to allow the debris or debris to be carried away without damaging the wound tissue.
5. Determine the wound area using a graduated ruler, measuring the longest vertical length (length) and the longest perpendicular length (width), multiplying both lengths.
6. Deposit the fibrin matrix · hyaluronic acid on the base of the wound depending on the size of the injury.
  - a) The necessary material for the handling and administration of the matrix is the following:
    - ✓ Sterile cloth
    - ✓ Sterile gloves
    - ✓ Sterile gauze
    - ✓ Normal saline solution (NaCl 0.9%), if necessary

- ✓ Straight blunt tip scissors
  - ✓ Simple sterile dissection clamp
  - ✓ Static demographic marker (Ref. 400133181)
- b) The matrix must remain in cold at all times (2 · 8xC)
  - c) Remove the mesh from the refrigerator
  - d) Ensure a sterile field before handling it
  - e) Keep in mind the area of the injury to calculate the required portion of the matrix
  - f) Open the container where the mesh is deposited once sterility is guaranteed
  - g) With the help of the demographic marker and the ruler included in the same package, mark the matrix area you need according to the area of the injury

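### Sections 9.1 and 9.5 give the weekly dose as a whole 21 cm² sheet with 7.5×10⁶ cells, but the sheet is adapted to a 5–10 cm² ulcer and may be trimmed, so the figure holds as the dose received only when nothing is cut off

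*Protocol*

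**What the plan says.** **The dose statement.** Section 9.1 schedules four administrations in which "one sheet will be administered weekly", describes the sheet as 21 cm² with 7.5×10⁶ ADSCs, and says that each patient in the experimental arm "will receive 4 slides at a concentration of about 360,000 cells/cm"². Section 9.5 closes with "The weekly dose to be received will be a" 21 cm² sheet carrying 7.5×10⁶ ADSCs.

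**The application instructions.** Section 9.5 wants the sheet placed so that it "covers the entire bed of the ulcer and the periphery", and says that the professional "will only have to adapt it to the area of the injury". Annex 2, step 6, has the matrix laid "on the base of the wound depending on the size of the injury". Its sub-steps tell the operator to:

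- 6e: "Keep in mind the area of the injury to calculate the required portion of the matrix"
- 6g: "mark the matrix area you need according to the area of the injury", using the marker and ruler supplied
- 6h: trim the matrix to the wound area, if that is needed
- 6i–6j: pick up that portion and place it so that it covers the injury and touches the wound bed.

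**The wound.** Inclusion criterion 3 (section 6.3) fixes the ulcer area at 5–10 cm².

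Neither 9.5 nor Annex 2 gives a width for the periphery, and Annex 2 does not mention the periphery.

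**The concern.** The protocol describes the same act in two ways. In 9.1 and the last line of 9.5, the patient receives a whole sheet. In the body of 9.5 and in Annex 2, the patient receives a piece sized to the ulcer. Both are true only when the sheet is left uncut. Since the sheet is at least twice the area of any eligible ulcer at entry, cutting is an obvious possibility.

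This matters because safety is a main objective of a phase I/II trial of a cell product. A safety result is read against an exposure. If the report says that patients tolerated four applications of 7.5×10⁶ cells, and some applications were trimmed pieces, the exposure is overstated for those applications. Later dose choices would then rest on a cell number that was not given.

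**Working it through.** **Inputs, all from the protocol.** Sheet area 21 cm², sheet content 7.5×10⁶ cells and density of about 360,000 cells/cm² (9.1); ulcer area at entry 5–10 cm² (6.3, criterion 3).

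**1. Reproduce the stated figure.** Density × area = 360,000 × 21 = 7.56×10⁶ cells. In reverse, 7.5×10⁶ / 21 = 357,143 cells/cm². The two densities agree within 0.8% (360,000 / 357,143 = 1.008), so the whole-sheet figure is consistent with itself.

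**2. Sheet against wound.** 21 / 10 = 2.1 and 21 / 5 = 4.2. The sheet is 2.1 to 4.2 times the ulcer area at entry.

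**3. Lower limit: cut to the wound, no margin.** Cells applied = density × wound area.

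| Ulcer area | Cells applied | Share of 7.5×10⁶ |
|---|---|---|
| 5 cm² | 5 × 360,000 = 1.8×10⁶ | 24% (by area, 5/21 = 23.8%) |
| 10 cm² | 10 × 360,000 = 3.6×10⁶ | 48% (by area, 10/21 = 47.6%) |

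This is a floor. Section 9.5 requires the periphery to be covered as well, so a piece cut exactly to the wound does not comply with 9.5.

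**4. Upper limit: untrimmed.** 100% of 7.5×10⁶ cells.

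**5. Between the limits, by margin width.** The protocol gives neither a margin nor an ulcer shape, so this step rests on an assumption: a circular ulcer with an even margin *m*, compared with the sheet by area only. Area covered = π(√(A/π) + m)², capped at 21 cm². Cells are taken at 357,143 per cm².

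| Assumed margin | 5 cm² ulcer | 10 cm² ulcer |
|---|---|---|
| 0.5 cm | 9.75 cm²; 3.48×10⁶ cells; 46% | 16.39 cm²; 5.85×10⁶ cells; 78% |
| 1.0 cm | 16.07 cm²; 5.74×10⁶ cells; 77% | 24.35 cm² needed, more than the sheet; 100% |

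The margin that uses the whole sheet is √(21/π) − √(A/π):

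- 5 cm²: 2.585 − 1.262 = 1.32 cm
- 10 cm²: 2.585 − 1.784 = 0.80 cm

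For a square ulcer, (√21 − √A)/2 gives 1.17 cm and 0.71 cm, so the shape assumption changes little.

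**6. What uses cell number.** The feasibility variable (10.1) counts patients who complete four administrations. The safety variable (10.1) is the incidence of adverse events and reactions, compared with the control group (1.11). Section 11 compares two arms. None of these takes the number of cells as an input.

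**The case against.** The strongest reply is that the 24–48% describes a case that the protocol rules out. Section 9.5 asks for bed and periphery, trimming in Annex 2 is conditional, and a plausible margin of about 0.8 to 1.3 cm uses the whole sheet. That stands. A reader might infer from the floor that patients will receive only a quarter to a half of the stated dose. The documents do not support this, because the share may be anywhere up to 100% and nothing shows how often trimming would happen.

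It can also be said that 9.1 already gives a density, which trimming leaves unchanged, and that wound length and width are measured at visits 2–5. Both are true. Together they give an approximate minimum exposure, but not the amount placed, and 9.5 still names the whole sheet as the dose received. The text reads as a rough translation, so the word for received may carry less weight than it seems to; however, 9.1 says administered, which points the same way.

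Three further readings are tempting and go too far.

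- **That 9.5 and Annex 2 contradict each other on coverage.** Covering the injury is compatible with covering bed and periphery. Annex 2 is silent on the periphery but does not forbid it.
- **That the area placed goes unrecorded.** The visit lists and the Annex 2 steps do not name it, but the schedule in Annex 1 is partly illegible and the data collection notebook is not shown.
- **That the overdose rule in 12.5.3 is left without a reference.** One full sheet is a clear ceiling.

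**Conclusion.** The point holds as an error in the stated dose. The figure of 21 cm² and 7.5×10⁶ cells is the content of the sheet supplied, and it is the dose received only when the sheet is not trimmed. At entry, the share applied lies somewhere between the 24–48% floor, which 9.5 excludes, and 100%. These limits use protocol figures only; the margin scenarios rest on an assumed ulcer shape and an even margin. Ulcer area after entry is not fixed by the document, so no figure is given for later applications.

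A reader might infer that the main results are biased. They are not affected by this point: neither the between-arm adverse event comparison nor the feasibility count depends on cell number, and the protocol plans no dose–response analysis. The effect is confined to the exposure to which the safety result is attributed. For a first safety assessment of a cell product, that is worth correcting, but it does not threaten the trial.

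**What to change.** - In 9.1 and 9.5, call 21 cm² / 7.5×10⁶ cells the maximum supplied per application, and state the dose applied as about 360,000 cells/cm² times the area of the piece placed.
- At visits 2–5, record the area marked at Annex 2 step 6g, or that the sheet was left untrimmed, and report exposure as cells applied.
- In Annex 2 steps 6g–6h, add the periphery to the area to be marked and fitted, to match 9.5.

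No single margin width is proposed. The documents give no basis for one, and an even 1 cm margin on a circular 10 cm² ulcer would need more than the sheet. Section 12.5.3 needs no change, since the full sheet remains the ceiling.

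The cost is some protocol wording and one data field at four visits, or no new field if the notebook already has it. Step 6g already has the operator mark the piece against a ruler, so the measurement is at hand. The downside is that the reported cell number may turn out lower than the protocol now states. Sample size, visits, product and endpoints stay as they are.
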